### Data collection

We will collect a wide range of quantitative and qualitative data to assess the effectiveness and cost-effectiveness and to evaluate the implementation of the intervention (see Fig 1 for complete overview of measurements). Questionnaires will be administered at baseline and 3, 6, and 12 months after baseline (Fig 1).

**Fig 1 pone.0289385.g001:**
[figure not shown]
Schedule of study procedures and assessments.

### Estimating the effectiveness of the intervention on trial outcomes

The primary outcome is time to first injurious fall. An injurious fall is defined as a fall resulting in wounds, bruises, sprains, cuts, medically recorded fractures, head or internal injury, requiring medical/health professional examination, accident and emergency treatment, or inpatient treatment [54]. This definition is consistent with moderate and serious injuries, as proposed by Schwenk (2012). Secondary outcomes include number of injurious falls, total number of falls, time to first fall resulting in any injuries (i.e., fall that results in minor, moderate, or severe injuries), total number of falls resulting in any injuries, time to first fall and (health-related) quality of life. Falls are defined as an unexpected event in which the participants come to rest on the ground, floor, or lower level [55]. At baseline, patients in both groups receive a falls calendar to keep track of falls, fall-related injuries, and fall-related healthcare use on a weekly basis for 12 months. The falls calendars will be returned every month by mail. Incomplete, missing or unclear data will be further inquired by telephone. Health-related) quality of life is assessed using the EuroQol-5D-5L (EQ-5D-5L) index value, EQ-5D visual analogue scale and the Older Persons and Informal Caregivers Survey Short Form (TOPICS-SF) summary score [56, 57]. EQ-5D-5L is a standardized instrument for measuring health-related quality of life [58]. The health states based on the five EQ-5D-5L domains will be converted to utility scores using the Dutch EQ-5D-5L tariff [56]. The TOPICS-SF is a 22-item questionnaire for measuring health-related quality of life, which was developed to evaluate patient-reported outcomes in the context of multidimensional geriatric care [57].

### Estimating the cost-effectiveness of the intervention

Societal costs related to the intervention and care as usual will be assessed using the institute for Medical Technology Assessment Medical Consumption Questionnaire (iMCQ) [59] and the institute for Medical Technology Assessment Productivity Cost Questionnaire (iPCQ; Fig 1) [60]. The iMCQ is a non-disease specific questionnaire for measuring health care use [59]. The iPCQ is a questionnaire for measuring productivity losses of paid work due to absenteeism, presenteeism and productivity losses related to unpaid work [60]. Costs will be calculated by multiplying the volumes of healthcare use with the corresponding unit prices. Lost productivity costs will be calculated using the friction cost approach.

### Process evaluation

The process evaluation will consist of two parts: a) assessing the feasibility of the intervention and b) evaluating how the intervention facilitates SDM.

### Process evaluation: Feasibility

To assess the feasibility of the intervention, we will collect the following: 1) data logged by the CDSS and patient portal, 2) participation data of the CDSS training, 3) physician satisfaction regarding the CDSS, 4) the Technology Acceptance Model (TAM; [61]) questionnaire; 5) the Website Satisfaction Scale questionnaire (WSS [62]), 6) videotaped consultations, 7) pharmacy records, and 8) falls calendar entries.

Usage data of the CDSS and patient portal will be measured throughout the study period. The extent to which the intervention was implemented as intended (fidelity/dose delivered) and the extent to which the participants actively engage with the intervention (dose received/exposure) will be assessed through data logged by the CDSS and patient portal, and the videotaped consultations. Dose received/exposure will also be assessed through participation data of the CDSS training. Reach/participation rate will be assessed through data logged by the CDSS to analyze the extent to which physicians propose changes in FRID prescriptions. Patients will be asked to self-report changes in medication use on the fall calendar on a weekly basis. These falls calendar entries and pharmacy records will be used to analyze the extent to which patients adhere to the physicians’ advice and changes in the treatment plan. Satisfaction with the intervention (dose received/exposure) will be measured through physician evaluations of the CDSS and the WSS questionnaire (patients). The TAM questionnaire assesses the perceived usefulness, perceived ease of use, and intended usage of the CDSS, and the WSS measures the comprehensibility, satisfaction and Emotional Support of the patient portal [62]. Finally, barriers and facilitators (context) will be assessed through the videotaped consultations, and physician evaluations of the CDSS by means of a survey.

### Process evaluation: Shared decision making

SDM will be measured through self-reported questionnaires in the full sample (i.e. perceived SDM; the iSHAREpatient and iSHAREphysician [63]. In addition, we aim to measure observed SDM in a subsample (n = 50) through videos of consultations (i.e. the Observer OPTION^MCC^ Multiple Chronic Conditions coding scheme [64]). SDM will be assessed in relation to two affective-cognitive outcomes: preparation for decision-making through the Preparation for Decision-making scale (PrepDM; [65]) and decisional conflict through the Decisional Conflict Scale (DCS; low literacy version; [66]). The ‘Question Format DCS– 10 item 3 response categories’ version of the DCS is recommended to be used for low literacy groups [67]. In addition, recall of information will be assessed in the subsample through the Netherlands Patient Information Recall Questionnaire (NPIRQ; [68]). The iSHARE questionnaire will be used to measure perceived SDM from both the patient and physician perspective. The NPIRQ consists of multiple-choice questions, completion items, and open-ended questions related to information about treatment and recommendations on how to handle side effects [68]. Patient responses on the questionnaire will be checked against the actual communication in video recordings of the consultations. In addition, the PrepDM will be used to assess how patients evaluate the usefulness of the patient portal and QPL for preparing themselves for communicating with their physician during the consultation. Finally, we will code observed shared (triadic) decision-making between the physician, the patient, and if relevant, the informal caregiver, in the videotaped consultations by using the Observer OPTION^MCC^ Multiple Chronic Conditions coding scheme [64].

SDM will be assessed using questionnaires in the full sample and video observations in a subsample. The subsample of 50 consultations in both intervention and control group will be video recorded to assess the level of SDM. After working with the CDSS for a couple of months, intervention-group physicians will be asked to fill out an online questionnaire about their satisfaction with the CDSS, to indicate whether they thought the advice provided by the CDSS was (sufficiently) accurate, if they perceived any barriers in using the CDSS system, and if they thought the patient perceived barriers in using the patient portal. Pharmacy records will be used to make an inventory of the prescribed medicines for individual patients at baseline and 12 months after baseline to assess adherence.

### Data management

Data will be handled confidentially and only a limited number of members of the study team will have access to the complete datasets. The collected and pseudonymized questionnaire data for each local center will be transferred to the Amsterdam UMC, where it will be entered, stored and processed in Castor. In addition, the digital CDSS and patient portal data will be stored locally at each hospital. Every 3–6 months, study data will be extracted to.csv text files and stored in a secured folder. Furthermore, administrative data will be stored in a secured SQL database. Finally, data from both control and intervention patients will be extracted from Epic every 3–6 months to.csv text files (e.g. medication data, problem lists, relevant lab values, and the prediction model variables). Data from individual patients will be pseudonymized, and the different datasets can only be linked through a participant identification number, which is stored in a separate data system. These data management systems all comply in accordance with the European Union General Data Protection Regulation.

### Statistical analysis

Data of the RCT will be analyzed according to the intention-to-treat principle. P-values of < 0.05 will be considered statistically significant.

### Estimating the effectiveness of the intervention on trial outcomes

For every participant, we will assess fall incidents during a fixed follow-up period of 12 months, which will start after a set 1 month, during which the dose of FRIDs will be stopped or decreased. Difference in time to injurious fall between the intervention and control group in the follow-up period will be analyzed by means of a multilevel Cox regression model based on hospital level [69]. Model fit will be assessed using standard approaches (e.g., the proportional hazards assumption with Schoenfeld residuals). We will adjust all models for age, sex and type of hospital, i.e. academic versus non-academic. In a sensitivity analysis, we will additionally adjust for significant baseline differences. Difference in total number of (injurious) falls in the follow-up period between the control and intervention groups will be analyzed by means of multilevel Poisson regression models based on hospital level. In the case of overdispersion, we will apply either quasi-Poisson regression or negative binomial regression depending on the observed distribution of the data. Difference between the intervention and control group with respect to time to any fall and time to fall that results in any injuries will be analyzed by means of survival analyses, similarly to the primary outcome.

Differences in EQ-5D-5L index score, EQ-5D visual analogue scale, and TOPICS-SF summary score between the intervention and control group after 12 months will be analyzed by means of linear mixed models. These models will be adjusted for the baseline value of the outcome [70].

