**Methods:**

A multicenter, cluster-randomized controlled trial with process evaluation will be conducted among hospitals in the Netherlands. We aim to include 856 individuals aged ≥ 65 years that visit the falls clinic due to a fall. The intervention comprises the combined use of a CDSS and a patient portal. The CDSS provides guideline-based advice with regard to deprescribing and an individual fall-risk estimation, as calculated by an embedded prediction model. The patient portal provides educational information and a summary of the patient’s consultation. Hospitals in the control arm will provide care-as-usual. Fall-calendars will be used for measuring the time to first injurious fall (primary outcome) and secondary fall outcomes during one year. Other measurements will be conducted at baseline, 3, 6, and 12 months and include quality of life, cost-effectiveness, feasibility, and shared decision-making measures. Data will be analyzed according to the intention-to-treat principle. Difference in time to injurious fall between the intervention and control group will be analyzed using multilevel Cox regression.

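### The 12-month fall analysis starts one month in, but the falls calendars cover only 12 months from baseline, and month-1 injurious falls drop out of the primary comparison

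*Protocol article*

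**What the plan says.** Two sections of the protocol article share the heading on estimating effectiveness, one within data collection and one within statistical analysis. They define the observation period differently.

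- **Analysis.** The statistical section assesses falls for every participant over "a fixed follow-up period of 12 months, which will start after a set 1 month", and describes that month as the one "during which the dose of FRIDs will be stopped or decreased". This period governs the Cox model for the primary outcome and the models for fall counts. The other time-to-fall outcomes are handled in the same way as the primary.
- **Recording.** The data-collection section states: "At baseline, patients in both groups receive a falls calendar to keep track of falls". The calendar covers falls, injuries and "fall-related healthcare use on a weekly basis for 12 months".
- **Abstract, Methods.** "Fall-calendars will be used for measuring the time to first injurious fall (primary outcome) and secondary fall outcomes during one year". No lag is mentioned.
- **Last scheduled contact.** "Questionnaires will be administered at baseline and 3, 6, and 12 months after baseline".
- **Endpoint.** "The primary outcome is time to first injurious fall". No time origin is given with this definition.
- **Principle.** "Data of the RCT will be analyzed according to the intention-to-treat principle".

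**The concern.** Time zero and the end of follow-up are part of the definition of a time-to-event endpoint. Here the stated analysis window runs one month past the stated recording period. Two analysts following the article could choose different origins, risk sets and censoring dates for the same primary outcome.

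The lag has a second consequence. It removes from the comparison the injurious falls of the month in which the intervention first acts on medication, so any early harm or early benefit is not counted. Participants who die or withdraw in that month add no time at risk, so the primary analysis is conditional on remaining under observation after allocation, in a trial where physicians and patients know the arm. The article also does not say whether someone injured in month 1 is still at risk for a first injurious fall when the clock starts.

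**Working it through.** **1. The windows, counted from baseline**

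| Source | Months covered |
|---|---|
| Analysis window (Statistical analysis) | 2–13 |
| Falls calendars (Data collection) | 1–12 |
| Abstract | one year, no lag |
| Last questionnaire | 12 |

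The overlap of analysis and calendars is months 2–12, that is 11 of 12 months. Month 13 is analysed but not recorded; month 1 is recorded but not analysed. Baseline cannot readily be read as the end of the lag month, because the Procedures section has the first questionnaires completed straight after the falls-clinic consultation.

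**2. The plan's own sample size**

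Inputs from the Sample size section: risks 0.22 and 0.12, two-sided 5%, 80% power, intraclass correlation 0.01, 10 clusters of 77, dropout 10%.

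- Design effect: 1 + (77 − 1) × 0.01 = 1.76.
- Individually randomised n per arm, unpooled variance: (1.960 + 0.842)² × (0.22 × 0.78 + 0.12 × 0.88) / 0.10² = 217.6. Times 1.76 = 383.
- Pooled variance: 221 × 1.76 = 389.
- Stated: 385 per arm, which lies between the two. Dropout: 770 / 0.90 = 856, as stated.
- Power at 385 per arm (effective 385 / 1.76 = 218.75): 79.7% pooled, 80.2% unpooled.

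The sample size therefore reproduces.

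**3. Effect of losing one month**

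Two assumptions that the article does not state: the 0.22 and 0.12 are 12-month risks, and hazards are constant.

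- Yearly hazards: −ln(1 − 0.22) = 0.2485 and −ln(1 − 0.12) = 0.1278 (ratio 0.51).
- 11-month risks: 1 − exp(−0.2485 × 11/12) = 0.2037 and 1 − exp(−0.1278 × 11/12) = 0.1106. Difference 0.093.

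| | 12 months | 11 months |
|---|---|---|
| Risks | 22.0% vs 12.0% | 20.4% vs 11.1% |
| Expected events, 385 per arm | 385 × 0.34 = 131 | 385 × 0.3143 = 121 |
| Power, pooled | 79.7% | 76.5% |
| Power, unpooled | 80.2% | 77.0% |

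The 121 keeps month-1 fallers at risk. If they were removed, the count would be 385 × [(1 − 0.0205) × 0.2037 + (1 − 0.0106) × 0.1106] = 119.

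**4. What month 1 holds**

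Month-1 risks are 0.0205 and 0.0106. Times 385, that is 7.9 control and 4.1 intervention, about 12 first injurious falls, or 12 / 131 = 9% of the 12-month total. This is not a further loss on top of the 10 events in step 3.

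**5. The price of starting the clock at baseline**

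Suppose the intervention has no effect at all in month 1. The 12-month intervention risk from baseline is then 1 − exp(−0.2485/12 − 0.1278 × 11/12) = 0.129, the difference is 0.091, and power is about 71% (pooled). This is the extreme case of dilution.

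**The case against.** **The endpoint can still be analysed.** A reader might infer that the primary endpoint cannot be computed. That is too strong. With calendars ending at month 12, participants would be administratively censored after 11 months, equally in both arms, and the Cox model can be fitted. What fails is the statement of a fixed 12-month period.

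**Intention-to-treat is not breached.** One might read the lag as contradicting that principle. It applies to every participant and moves nobody out of the allocated arm. What remains is a tension: post-allocation events, and people lost in month 1, are left out of the primary comparison.

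**Month-1 fallers.** It is tempting to say that a patient injured in week 2 enters as event-free. The article does not say so; it says nothing either way, and an analysis plan not shown may settle it.

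**The lag has a rationale.** The statistical section ties it to the month in which medication is changed, and step 5 shows that a baseline start can cost more power than the missing month. With calendars to month 13, constant hazards and month-1 fallers kept at risk, the lagged window gives the same 131 events, so the lag alone costs no power. This stands, and makes the choice of primary origin a matter of judgement.

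**Missing sources.** The schedule figure and full protocol are not shown and might give a longer calendar period. The sections of the article would still disagree with one another.

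**Conclusion.** The inconsistency is real and sits in the running text: the abstract and the data-collection section support 12 months from baseline, while the statistical section needs months 2 to 13. On the text shown, 11 months of the stated window are covered, for the primary outcome and every other fall outcome.

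The numerical cost is modest: about 10 fewer expected events and about 3 points of power. It rests on constant hazards and on reading 0.22 and 0.12 as 12-month risks. If those figures were meant for whatever window is finally analysed, this loss disappears. The sample-size calculation itself is not at fault. The weightier issues are that the time origin and end of the primary endpoint are not consistently fixed, and that early injurious falls, about 12 under the same assumptions, are outside the primary comparison with no stated report by arm.

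**What to change.** Reconcile the abstract, the data-collection section and the statistical section on time origin and calendar length, by one of two routes.

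1. **Baseline origin as primary.** Start the clock at the baseline falls-clinic visit and end at 12 months, with every recruited participant at risk from day 0. Keep the 1-month-lag analysis as a pre-specified sensitivity analysis. The calendars already cover this, so the change is one of wording. The cost is dilution if the effect begins only after month 1, bounded by step 5.
2. **Lag as primary.** Run the calendars to month 13, or state an 11-month window and restate the power. Pre-specify a baseline-origin intention-to-treat sensitivity analysis. The cost is one more calendar month per participant, or the roughly 3 points of power.

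Under both routes, report month-1 injurious falls, deaths and withdrawals by arm, and state whether a participant with an injurious fall in month 1 remains at risk in the lagged analysis. The article describes recruitment as ongoing, so the choice should be made while participants are still being followed: month-13 falls that were never recorded cannot be reliably recovered later.

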### Sample size

Sample sizes of *n* = 385 in the intervention and *n* = 385 in the control group (10 clusters with 77 patients in each cluster) are needed to detect a difference in proportion of injurious falls of 0.10 with 80% power. We inferred the proportion of patients who will experience an injurious fall to be 0.22 in the control and 0.12 in the intervention group. In these calculations, we assumed the two-sided significance level of 5% and an intraclass correlation coefficient of 0.01 to account for clustering [71]. Presupposing a drop-out rate of 10%, 856 patients will need to be included.

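### With ten hospitals, the usual large-sample test of the multilevel Cox effect would have about 8-10% type I error at the planned ICC, and a small-cluster test leaves about 67% power instead of 80%

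*Protocol article*

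**What the plan says.** All points are in the protocol article.

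- **Primary analysis** (Statistical analysis, Estimating the effectiveness of the intervention on trial outcomes): the between-arm difference in time to injurious fall "will be analyzed by means of a multilevel Cox regression model based on hospital level". All models are adjusted for age, sex and academic versus non-academic hospital.
- **Significance rule** (Statistical analysis): "P-values of < 0.05 will be considered statistically significant".
- **Counts of falls** (same effectiveness subsection): multilevel Poisson models at hospital level; if there is overdispersion, "we will apply either quasi-Poisson regression or negative binomial regression depending on the observed distribution of the data". The fallback sentence does not repeat that the model is multilevel.
- **Sample size**: 385 evaluable patients per arm, drawn from ten hospitals of 77, "are needed to detect a difference in proportion of injurious falls of 0.10 with 80% power". The planning risks are 22% under usual care and 12% with the intervention. On error rate and clustering the section states: "we assumed the two-sided significance level of 5% and an intraclass correlation coefficient of 0.01 to account for clustering".
- **Allocation** (Randomization and blinding): whole hospitals are allocated. Two are placed by default, one in each arm, and the rest are randomised 1:1, stratified by academic status.

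The article names no reference distribution, degrees of freedom or small-sample method for the hospital-level effect.

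**The concern.** Treatment varies only between hospitals, so the information on its effect is limited by ten hospitals, however many patients each one recruits. Two things go wrong if such an effect is tested in a random-effects survival model with a normal or chi-square reference.

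1. The standard error depends on a between-hospital variance estimated from few units, so a t reference on few degrees of freedom is closer to the truth than z.
2. Maximum likelihood tends to underestimate that variance and often puts it at or near zero. The analysis then behaves as if there were no clustering.

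Both effects narrow the confidence interval for the primary hazard ratio and raise the false-positive rate above the intended 5%. A nominal p just under 0.05 would be weaker evidence than it appears. The usual correction widens the critical value, and the sample size has to allow for that.

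**Working it through.** **1. Reproducing the plan's sample size.** Inputs from the Sample size section: 0.22 versus 0.12, two-sided 5%, 80% power, ICC 0.01, 77 patients per hospital, 10 hospitals.

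- Individually randomised n per arm, unpooled variance: (1.96 + 0.8416)² × (0.22×0.78 + 0.12×0.88) / 0.10² = 217.6. With pooled variance it is 221.
- Design effect: 1 + 76 × 0.01 = 1.76.
- 217.6 × 1.76 = 383; 221 × 1.76 = 389. The stated 385 lies between them.
- 770 / 0.90 = 855.6, so 856, as stated.

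The plan's figure therefore reproduces with normal quantiles and has no allowance for few clusters. The continuity-corrected form gives 422 and does not match.

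**2. Degrees of freedom.** The hospital-level terms are intercept, arm and hospital type: 10 − 3 = 7 df. Without hospital type there would be 8.

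**3. Simple bound on the error rate.** Comparing a t statistic with 1.96 gives 2 × P(t₇ > 1.96) = 9.1%, or 8.6% with 8 df.

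**4. Simulation under no effect.** Ten hospitals, average size 77, 22% risk in both arms, arm and hospital type as hospital-level terms. The ICC is converted to a log-hazard SD: √(0.01×0.22×0.78) / (0.78 × 0.2485) = 0.214 at ICC 0.01. The Cox model uses a Gaussian hospital intercept (Laplace ML, 2,000 runs per row). The Poisson/exponential-hazard model uses a normal hospital intercept (quadrature ML, 3,000 runs per row). Monte Carlo standard error is about 0.6 points.

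| Model, hospital sizes | ICC | Wald z | LR test | t(7) | Variance near zero |
|---|---|---|---|---|---|
| Poisson, equal | 0 | 4.5% | 4.1% | 1.5% | 84% |
| Cox, equal | 0.005 | 7.5% | – | 3.7% | 53% |
| Poisson, equal | 0.005 | 7.8% | 6.8% | 3.6% | 63% |
| **Cox, equal** | **0.01** | **9.2%** | – | **4.3%** | 36% |
| **Cox, size CV 0.5** | **0.01** | **8.4%** | – | **4.2%** | 39% |
| **Poisson, equal** | **0.01** | **9.6%** | **8.3%** | **5.0%** | 45% |
| **Poisson, size CV 0.5** | **0.01** | **10.4%** | **9.2%** | **5.9%** | 49% |
| Cox, size CV 0.5 | 0.02 | 10.8% | – | 5.0% | 22% |
| Poisson, equal | 0.02 | 11.5% | 9.8% | 6.6% | 24% |
| Cox, size CV 0.5 | 0.03 | 11.3% | – | 6.1% | 13% |
| Poisson, equal | 0.05 | 14.7% | 10.9% | 8.2% | 6% |

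Only ICC 0.01 comes from the protocol; the other ICCs are assumed. Two more Poisson runs at ICC 0.01 (17% risk; two academic hospitals instead of four) gave 9.7% and 9.8% with z, 7.8% and 8.5% with the likelihood-ratio test, and 4.2% and 4.9% with t(7). One further frailty simulation gave about 10.8% with z and 6.0% with t(7), slightly above these ranges. In a separate exponential-frailty simulation without the hospital-type term, a t-test on hospital-level log rates gave 4.4-5.1% across ICC 0.01 to 0.05.

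**5. Power once the test is corrected.** The standard error of the risk difference is √0.2772 × √(1.76/385) = 0.5265 × 0.0676 = 0.0356, so the noncentrality is 0.10 / 0.0356 = 2.81.

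- Normal reference: Φ(2.81 − 1.96) = 80%.
- t on 7 df (critical value 2.365): 67.5%.
- t on 8 df (critical value 2.306): 69.3%.

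Regaining 80% with the same ten hospitals takes 145 evaluable patients per hospital on 7 df (1,450 in all) or 131 on 8 df (1,310 in all), against 770 planned.

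**6. Count fallback.** If the hospital level were dropped and the ICC for counts were also 0.01 (an assumption), the type I error would be 2 × [1 − Φ(1.96/√1.76)] = 14%.

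**The case against.** The strongest reply is that the article is silent on this detail. It names a model and a threshold, but no Wald z test, no estimation method and no reference distribution. Degrees of freedom are commonly left to the statistical analysis plan, which is not shown, and what the article does fix, an analysis at the level of randomisation, is right. That stands against any claim that the plan uses no correction, so the error rate can only be stated conditionally.

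It does not dispose of the point, because the Sample size section is in the article. Its 385 per arm rests on normal quantiles. If the analysis plan adds a t(7) reference, the stated 80% power no longer follows from the stated inputs; if it does not, the 5% level is not kept.

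Three stronger readings are tempting and not supported:

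- **A reader might infer a false-positive rate of 8-13% as a fact about this trial.** The part from about 11% upwards needs ICCs of roughly 0.02 to 0.05, and the protocol assumes 0.01. At ICC 0 there is no inflation.
- **A reader might infer that the count fallback drops the hospital level.** The text does not say so. A natural reading is that only the variance function changes within the multilevel model. The wording is merely open.
- **A reader might infer that quasi-Poisson cannot carry a hospital random effect.** Penalised quasi-likelihood routines fit such models, so this is no ground for objection.

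**Conclusion.** The point holds conditionally. If the multilevel Cox effect is judged by the usual large-sample z or likelihood-ratio test, type I error with ten hospitals is about 8-10% at the protocol's own ICC of 0.01, not 5%. If a t reference on 7 df is used, the error is about 4-6% at that ICC, but the planned size gives about 67% power. On the protocol's inputs and its comparison of proportions, the 5% level and the 80% power do not both hold.

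The figures rest on these assumptions: ML estimation of the hospital variance; four academic hospitals in the main runs (the number is not given, and two gave the same result); all ten hospitals treated as randomly assigned although two were placed by default; and no age or sex effects simulated. The power figures use the planned difference in proportions, not a Cox calculation.

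The count-model point is smaller. It concerns secondary outcomes and needs one clarification.

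**What to change.** 1. State that the primary p-value and confidence interval use a small-cluster method, fixed before analysis. Either test the multilevel Cox estimate against t on 7 df (10 hospitals minus intercept, arm and hospital type), or use a two-stage analysis: age- and sex-adjusted log rates per hospital, compared by arm with adjustment for hospital type, also on 7 df. The two-stage form is safer if the ICC may exceed 0.01, because t(7) with an ML variance drifted to 6.6% at ICC 0.02 and 8.2% at 0.05 in the Poisson runs.
2. Restate the power in the Sample size section with the same reference: about 67% at 385 per arm, or the larger number needed for 80%.
3. State that the overdispersed count model keeps the hospital level, for example negative binomial with a hospital random intercept.

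**Cost.** Items 1 and 3 need wording and modest programming. The critical value rises from 1.96 to 2.36, so the interval is about 2.36/1.96 = 1.2 times as wide for the same standard error. The real cost is the lower stated power: recovering 80% with ten hospitals would take about 1,450 evaluable patients on 7 df, nearly twice the 770 planned.
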